## Abstract

**Background:**

In Finland, the ‘day activity service’ is targeted at older home care clients who are unable to participate in other available activities due to poor health or functional disabilities. The aim of the day activity service is to support home care client’s ability to live at home and to enhance their wellbeing and social inclusion. This mixed method study examines the effectiveness, cost-effectiveness and process of the day activity service.

**Methods:**

The target sample size is 200 participants. The intervention group (*n* = 100) is composed of home care clients who begin to participate in the day activity service. The comparison group (*n* = 100) are home care clients who do not participate in the day activity service, and whose functioning and care needs are similar to the participants of the intervention group. The primary outcome is social inclusion (ESIS-scale). Secondary outcomes are loneliness (single item and De Jong Gierveld Loneliness Scale) and social care related quality of life (ASCOT). Baseline, three-month and six-month follow-up surveys are gathered from intervention and comparison group participants in order to compare outcomes between groups pre- and post-intervention.

Costs of health and social services, based on administrative data, and the costs of the intervention are utilized in examining the cost-effectiveness of the intervention with the above-described measurements. Qualitative data are collected by interviewing the intervention participants (*n* = 10) and professionals working at the day activity centres and older people’s services (4 focus groups) to explore the perceived outcomes and process of the intervention to find out how and why the intervention is effective or ineffective.

**Discussion:**

The study seeks to produce a comprehensive understanding of the effectiveness, cost-effectiveness and implementation process of the day activity service.

**Trial registration:**

ISRCTN13146087, Registration date 03/04/2022.

## Background

In recent decades, living independently has become high valued and guiding principle of ageing policies [1]. Consequently, in Finland and in other European countries, home-based care has become the primary service of supporting older people’s daily life. At the same time, low resources in formal home care and older home care client’s increased disadvantages and care needs have led to experiences of the inadequacy of support and services [2, 3]. Even though living in familiar surroundings has many positive consequences [4], residential stability may not always be beneficial if the older person is bound to a place where wellbeing and sense of security are challenged in different ways [5, 6].

In the Finnish legislation, municipalities or federations of municipalities (after January 2023: wellbeing service counties) have been obligated to organize home care for older people [7, 8], but the producers of these care services may also be private companies and third sector organizations. Formal home care includes personal or virtual visits and support services, such as meal services, cleaning services and safety services. Formal home care has focused mostly on clients’ physical needs and resources [9], while home care clients have unmet needs related to social activities [10], which, combined with limited and inadequate home care services, may lead to different forms of social exclusion. In Finland, social exclusion of older home care clients has been addressed by a group-based intervention called *day activity service*. The day activity service is an additional non-statutory service produced mainly by municipalities or federations of municipalities.

The day activity service has been widely used in formal home care services, yet systematic research evaluating the service in the Finnish context has been non-existent. The day activity service is often conducted in day centres where other activities are also available for older people who are not in need of formal home care. Previous studies in other countries have shown that day centres may be beneficial in supporting older people to live at home for longer [11]. However, little is known about the effectiveness and cost-effectiveness of day activity groups targeted at older home care clients.

The primary aim of the day activity service is to support home care clients living at home by promoting their health and wellbeing, maintaining their physical, psychological, and social functional ability, and enhancing social inclusion. As this study is part of the SOLDEX (Old-age social exclusion in home care: Prevalence, meanings and intervention) project [12], we focus on examining the day activity service from the perspective of social inclusion. In addition, we are interested in the social functional ability and comprehensive wellbeing related to the day activity service.

The study is carried out following the UK Medical Research Council framework of the evaluation of complex interventions [13, 14]. The day activity service can be defined as a complex intervention; therefore, we systematically evaluate both effectiveness and process of the intervention (see [14]). The study focuses on examining the outcomes of the intervention in terms of social inclusion, loneliness and social care related quality of life. The effectiveness and cost-effectiveness will be examined using a pragmatic quasi-experimental design because the day activity service is already in use. By integrating qualitative methods into the trial design, we plan to investigate how and why the intervention works or does not work more in depth (see [15]). From the perspective of process evaluation, it is possible to examine several issues such as the implementation of the intervention or mechanisms of impact [16]. In this study, we will focus on the process of the intervention delivery by examining facilitators and barriers of its implementation. The program theory of the day activity service is somewhat unknown; thus, the process evaluation will also explore understandings of the program theory [14, 17]. This will help to develop an understanding of how the intervention might be implemented in other contexts, if shown to be effective. In addition, we will examine perceived and unexpected outcomes both quantitatively and qualitatively.

### Objectives

The general aim of the study is to produce knowledge on the effectiveness, cost-effectiveness and the implementation process of Finnish day activity services targeted at older home care clients. The specific research questions are:What are the effects of the day activity service in terms of social inclusion, loneliness, and social care related quality of life?What are the costs and cost-effectiveness of the day activity service compared to care without the day activity service?What are the facilitators and barriers related to the implementation of the intervention?What are the perceived and unexpected effects of the day activity service?

## Methods

### Overall study design and setting

This mixed method pragmatic quasi-experimental trial will examine the effectiveness, cost-effectiveness, and process of an existing intervention called *day activity service*. The overall study design is described in Fig. 1. The effectiveness is evaluated with quantitative quasi-experimental design by comparing a group of home care clients taking part in the intervention (IG) with a group of home care clients with similar characteristics not taking part in the intervention (CG). The study is a pragmatic trial, as the day activity service is an existing intervention carried out in ordinary circumstances as part of formal home care services [18]. The trial is quasi-experimental, because randomization is not an option due to the fact that the intervention is already in use. Baseline, three-month follow-up, and six-month follow-up surveys are collected from IG and CG participants. The cost-effectiveness evaluation is based on the quasi-experimental trial design and the administrative data of the social and health care service use. The process evaluation is mainly based on qualitative data that is collected by interviewing the IG participants and the professionals working at the day activity service and formal home care.

**Fig. 1 Fig1:**
[figure not shown]
Flow diagram of the study design

The study is conducted in Finland in one municipality and one social welfare and health care joint authority consisting of seven municipalities. There are approximately 2300 older home care clients in the research areas. As of January 2022, 210 of the older home care clients in the research areas had been granted access to the day activity service. According to the professionals responsible for the day activity service, the number of participants has somewhat reduced during COVID-19 pandemic. The research areas include both urban and rural residential districts. The day activity service is carried out across 12 municipalities, villages, or residential areas.

### Description of the intervention

The intervention is targeted at older home care clients who are not able to participate in other activities because of their poor health or functional ability. The day activity service is a complex intervention which means that it has multiple aims and there is variation in how it is carried out in different settings. The principle aim of the day activity service is to support the older home care clients’ ability to live in their own homes by promoting their health and wellbeing, maintaining their physical, psychological, and social functional ability and by enhancing social inclusion. More specifically, the intervention has aims to; maintain memory, promote social interaction, provide peer support, and reduce loneliness and sense of insecurity.

The day activity service is an additional service to the regular home care services and takes place in local day activity centres or other places once a week. It is a group-based intervention, and the duration of one meeting is from 2 to 6 hours. The intervention includes rehabilitative and preventive activities such as physical exercising, outdoor activities, thematic discussions, activating memory, listening to music, having lunch and coffee together with group participants. The day activity service is tutored by practical nurses or home helpers. In the study sites, there are day activity groups of 2 hours, 3 hours, 4 hours, and 6 hours. There is also variation in the content and activities of the intervention. A payment per meeting is between 5 to 23 euros depending on the duration of the service. Transport is arranged if necessary, paying for a local bus ticket.

Home care clients need to apply for the service and get a service decision on it to take part in the day activity service weekly. The criteria for the decision are i) not able to participate in other activities produced by municipalities, private sector or third sector, and ii) is capable of attending group activities. Severe memory disorder can prevent participation, for example.

### Quasi-experimental trial

#### Participants, selection criteria and recruitment

The target sample size for the intervention study is 200 participants (100 IG + 100 CG) based on previous research with similar study designs (e.g., [19]) and directional sample size calculations. We accepted an alpha risk of 0.05% and a power of 80% at an effect size of 0.5. A theoretical sample of 64 participants in the IG and 64 participants in the CG will be needed. Finally, we assumed that potential attrition rate may be 20–30% due to the functional decline of the participants.

The IG is composed of home care clients aged 65 years or older who are new participants in the day activity service. All new participants of the day activity service are eligible for the IG. The participants are recruited with the help of personnel who are responsible for the official decisions of the day activity service. Personnel or researchers will call older people in receipt of service decisions to access the day activity service and invite them to participate in the study. Researchers will receive the contact details of the day activity service participants from the personnel. Information about the study, an informed consent form and the first questionnaire are sent to those home care clients who agree to participate in the study when calling them. IG participants fill the informed consent form and baseline survey before beginning to participate in the day activity service.

The CG consists of home care clients aged 65 years or older who do not participate in the day activity service, and whose functioning and health are similar to the participants of the IG. Possible reasons for non-participation include being on the waiting list and not knowing about the service. The CG participants are recruited from the sample of home care clients who attend the other part of the research project from May to October 2022 (see [12]). The sample (target *n* = 1700) of home care clients respond to the same survey used as baseline survey in the quasi-experimental trial. The formation of the CG proceeds in three steps. 1) Potential CG participants are chosen based on the questions and measurements of the survey. The primary indicator is the question: Do you participate in group activities or hobby activities? Those who respond “No, but I would like to participate” are selected as potential CG participants at first stage. 2) After that, the potential respondents for the CG are compared with the respondents who have recently started to attend the day activity service. Comparison is conducted using general indicators related to their functioning and health, such as quality of life (Euro-HIS-8) and perceived health. 3) The invitation and follow-up surveys are sent to 130 home care clients whose functioning and health are as similar as possible to those clients attending the day activity service.

The recruitment of IG participants begins in August 2022 and continues until the target sample size is achieved. The estimated recruitment rate is 14 new study participants per month; therefore the recruitment phase may last until March 2023.

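### The printed alpha of 0.05% does not give the stated 64 per group; 64 follows from a two-sided 5%, so the alpha is very probably misprinted

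*Protocol article*

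**What the plan says.** The sample-size justification is in the protocol article under Quasi-experimental trial, Participants, selection criteria and recruitment. The target is 200 participants, 100 in each group, based on earlier studies of similar design and on "directional sample size calculations".

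The inputs are given in one sentence: "We accepted an alpha risk of 0.05% and a power of 80% at an effect size of 0.5". The result follows: "A theoretical sample of 64 participants in the IG and 64 participants in the CG will be needed". The paragraph then allows for losses: "we assumed that potential attrition rate may be 20–30% due to the functional decline of the participants".

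The paragraph does not say whether the test is one- or two-sided, and it does not name the type of effect size. The article states an alpha and a power nowhere else. The Statistical analysis section of the trial gives no significance level and does not refer back to this paragraph.

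**The concern.** An alpha of 0.05% is 0.0005, far stricter than the level normally paired with 80% power and an effect size of 0.5. The combination of 80% power, effect size 0.5 and 64 per group is what a two-sample comparison gives at a two-sided 5%. The printed alpha and the printed sample size therefore look incompatible.

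This is the only type I error rate in the article, and it sits in the only justification of the sample size. Nothing elsewhere corrects it, so a reader can recover the intended value only by redoing the calculation. If the trial is later reported at 5%, anyone comparing the report with this article will find an unexplained hundredfold difference in the stated error rate.

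**Working it through.** **Inputs, all from the sample-size paragraph**
- alpha as printed: 0.05% = 0.0005
- power: 80%
- effect size: 0.5, taken here as a standardised mean difference d (assumption; the type is not named)
- allocation: 1:1, 64 per group
- attrition: 20–30%
- target: 100 per group
- sidedness: not stated, so both were tried

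**Formula.** For two equal groups, the normal approximation is

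n per group = 2 (z_alpha + z_power)² / d², with z_power = 0.8416 and 2/d² = 2/0.25 = 8.

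Each result was cross-checked with the two-sample t-test (noncentral t), which is slightly larger.

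**Reproducing the plan's 64**
- Two-sided 5%: z_alpha = 1.9600; 8 × (1.9600 + 0.8416)² = 8 × 7.849 = 62.8, so 63. The t-test gives 63.77, so 64. This matches.
- One-sided 2.5% uses the same critical value and also gives 64.

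**The printed alpha and the remaining variant**
- Two-sided 0.05%: z_alpha = 3.4808; 8 × (3.4808 + 0.8416)² = 8 × 18.68 = 149.5, so 150. The t-test gives 152.5, so 153.
- One-sided 0.05%: z_alpha = 3.2905; 8 × (3.2905 + 0.8416)² = 8 × 17.07 = 136.6, so 137. The t-test gives 139.3, so 140.
- One-sided 5%: z_alpha = 1.6449; 8 × (1.6449 + 0.8416)² = 8 × 6.183 = 49.5, so 50. The t-test gives 50.2, so 51.

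| alpha | sides | n per group (normal) | n per group (t-test) | power at 64 per group (t-test) |
|---|---|---|---|---|
| 0.05% (as printed) | two | 150 | 153 | 24% |
| 0.05% (as printed) | one | 137 | 140 | 30% |
| 5% | two | 63 | 64 | 80.1% |
| 5% | one | 50 | 51 | 88% |

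The power column can be checked by hand with Φ(d√(n/2) − z_alpha). At n = 64, d√(n/2) = 0.5 × √32 = 2.828. For two-sided 0.05%, Φ(2.828 − 3.481) = Φ(−0.652) = 0.26, against 0.24 by the t-test. For two-sided 5%, Φ(2.828 − 1.960) = Φ(0.868) = 0.81, against 0.801.

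The ratio of the two alphas is 0.05/0.0005 = 100.

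**Attrition step**
- 20%: 64/(1 − 0.20) = 80 per group
- 30%: 64/(1 − 0.30) = 91.4, so 92 per group

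Both are below 100. Conversely, 100 per group leaves 80 after 20% loss and 70 after 30% loss, both above 64.

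**The case against.** The strongest reply is that this is a slip of notation, with 0.05 printed as 0.05%, and that nothing in the design depends on it. Most of that stands. At a two-sided 5% the 64 is right, the attrition allowance fits within the target, and neither recruitment nor the choice of analysis methods changes. The sentence is still wrong as printed. An analysis plan that is not shown might excuse an omission, but it does not excuse a figure that contradicts the result beside it.

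A reader might draw three stronger conclusions, which the document does not support.

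- **That the trial is underpowered.** The 24% applies only if the data were really tested at 0.0005. The 64 shows that the calculation almost certainly used 5%. The low figure proves a mismatch and nothing more.
- **That a result of, say, p = 0.01 would not count as positive.** The alpha appears as a planning input. The Statistical analysis section sets no p-value rule, so this consequence is not in the text.
- **That the word *directional* makes a second contradiction**, because a one-sided 5% needs only 51. The word can mean one-sided, but beside the reference to earlier studies it reads at least as naturally as *indicative*. It is ambiguous wording.

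The arithmetic also cannot settle sidedness on its own, because one-sided 2.5% gives the same 64. Two-sided 5% is the likely reading, and the authors need to confirm it.

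**Conclusion.** The point holds as an internal inconsistency in the stated error rate. With alpha 0.05%, 80% power and effect size 0.5, the required number is about 153 per group two-sided or 140 one-sided, more than twice the stated 64. Neither sidedness rescues the printed alpha. Of the variants tried, only two-sided 5%, or its one-sided 2.5% equivalent, returns 64, so the printed alpha is very probably too small by a factor of 100.

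This rests on two assumptions: that 0.5 is a standardised mean difference, and that the calculation was a simple two-group comparison of means with equal allocation. The exact match at two-sided 5% supports both, but the article states neither. The adequacy of the planned sample is not in question on the article's own assumptions.

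**What to change.** Correct the alpha to 5% (0.05). In the same sentence, have the authors confirm and state the sidedness (two-sided 5% is the reading that fits 64) and that 0.5 is a standardised mean difference. If *directional* was meant as *indicative*, say so; if it was meant as one-sided, reconcile it with the 64.

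It would help to show the attrition step. Subject to the authors' confirmation, the passage could read: with a two-sided alpha of 0.05 (5%), 80% power and a standardised mean difference of 0.5, 64 participants per group are required; allowing for 20–30% attrition this becomes 80–92 per group, and the target is set at 100 per group.

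The cost is one corrected sentence and a short check with the authors. Enrolment, design and analysis do not change.

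### The group-activity filter is applied to the comparison group only, so intervention members who would answer differently may have no comparator, and weighting the full intervention group cannot balance this item

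*Protocol article*

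**What the plan says.** The rules for forming the two groups are in the Protocol article under 'Participants, selection criteria and recruitment'.

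- **Comparison group.** Step 1 rests on one survey item: "The primary indicator is the question: Do you participate in group activities or hobby activities". Only respondents who do not take part now but would like to "are selected as potential CG participants at first stage". Step 2 then compares candidates with recent service starters: "Comparison is conducted using general indicators related to their functioning and health, such as quality of life (Euro-HIS-8) and perceived health". Step 3 invites the 130 who are most similar in functioning and health.
- **Intervention group.** "All new participants of the day activity service are eligible for the IG", given age 65 or older. No condition is placed on the activity item.
- **Measurement.** The item is available in both groups. The CG source sample is said to "respond to the same survey used as baseline survey in the quasi-experimental trial", and "IG participants fill the informed consent form and baseline survey before beginning to participate in the day activity service".

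Entry to the service itself is described under 'Description of the intervention'. "Home care clients need to apply for the service and get a service decision on it", and the first criterion for that decision is being "not able to participate in other activities produced by municipalities, private sector or third sector".

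Under 'Statistical analysis' for the trial, intention-to-treat is primary for all outcomes, and propensity score weighting is named as one possible method for handling non-randomisation, to be used if needed.

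**The concern.** At baseline every CG member has the same value on the item: no current group or hobby activity, and a wish for it. IG members may have any value. Existing activity and the wish for more plausibly bear on social inclusion (the primary outcome) and loneliness (secondary). An IG member who already has a hobby group may have less to gain or may swap one activity for another. One without a wish of their own may attend little. If such members are present, the IG–CG contrast mixes the effect of the service with a difference in prior activity and motivation, and the same mixture enters the ICER.

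The remedy named for non-randomisation does not reach this item while the whole IG is kept. The CG has only one answer level, so there is nobody in it to weight up for the other answers.

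**Working it through.** **1. The selection rules side by side**

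| Feature | IG | CG |
|---|---|---|
| Answer to the activity item | Any | One answer only |
| Unable to join other organised activities | Required by the service decision | Not assessed |
| Own wish for group activity | Suggested by the application, not stated | Required by the answer |
| Hobby or informal activity outside organised provision | Not covered | Excluded by the answer |
| Functioning and health | As they come | Chosen to resemble service starters |

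The service criteria work in the same direction as the CG filter but measure something different. Being unable to join organised provision is not the same as having no hobby activity and wanting some.

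**2. What weighting can do**

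If the item is put in the propensity model, any other answer predicts IG membership with certainty, and no CG member can stand in. If it is left out, the imbalance stays. Trimming or overlap weights would deal with it only by dropping those IG members, which is restriction under another name.

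**3. Size of the possible shift**

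Shift in the contrast = s × δ, where s is the share of the IG with another answer and δ is their outcome difference in SD from the rest of the IG. Both are assumptions; the documents give neither.

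| s | δ = 0.2 | δ = 0.3 | δ = 0.5 |
|---|---|---|---|
| 0% | 0 | 0 | 0 |
| 10% | 0.02 | 0.03 | 0.05 |
| 30% | 0.06 | 0.09 | 0.15 |
| 50% | 0.10 | 0.15 | 0.25 |

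At δ = 0.3, s = 10–30% gives 0.03/0.5 = 6% to 0.09/0.5 = 18% of the planned effect. The direction depends on which answers occur.

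A simulation with true effect zero and δ = 0.3, weighting the CG to the IG on health, left a bias of 0.031 SD at s = 10% and 0.091 SD at s = 30%. Restricting the IG to the CG's answer brought it to about 0 (0.001 and −0.001).

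**4. Power if the IG is restricted**

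The plan's figure first: effect size 0.5, power 80% and a two-sided t-test at 0.05 give 64 per group, as stated. (The article prints the alpha with a percent sign; 64 is reproduced only at 5%.) Allowing for attrition, 64/0.8 = 80 and 64/0.7 = 91.4, rounded up to 92, both within 100.

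For the restricted comparison with 100 + 100 enrolled and attrition a, n(IG) = 100(1 − s)(1 − a) and n(CG) = 100(1 − a). Power at 0.5 SD, two-sided 0.05:

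| s excluded | a = 20%: n, power | a = 30%: n, power |
|---|---|---|
| 0% | 80 v 80, 88.2% | 70 v 70, 83.6% |
| 10% | 72 v 80, 86.4% | 63 v 70, 81.5% |
| 20% | 64 v 80, 84.2% | 56 v 70, 79.0% |
| 30% | 56 v 80, 81.3% | 49 v 70, 75.9% |
| 50% | 40 v 80, 72.6% | 35 v 70, 66.7% |

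Power of 80% needs 53 IG completers at 20% attrition (53/0.8 = 66.25 enrolled, so about 34% can be excluded). At 30% attrition it needs 59 (59/0.7 = 84.3, so about 16%).

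**The case against.** A reader might infer that background activity differs between the groups by design. The documents do not support that. Every IG member has applied for the service and been judged unable to join other organised activities, so both groups are selected, by different routes, on lacking activity and seeking it. If every IG member would give the CG's answer, the shift is zero. Nothing in the text shows that members without a wish of their own exist. This part of the objection stands: a difference is possible, not fixed.

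A reader might also infer that no analysis can repair the problem. That goes too far. The item is measured in both groups before the service starts, so restriction to the common answer, followed by weighting on other covariates, removes the imbalance on this item. The article leaves room for other methods and says under 'Strengths and limitations' that baseline differences will be considered. Covariate lists and common-support rules may well sit in an analysis plan not shown. But the selection rules are fixed here, and no later plan can supply comparators that recruitment excluded.

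Three further points stand in part. The step 2 indicators are given as examples, so other indicators may be used, but the CG would still have only one answer to this item. IG members answer after their service decision, so the same words may not mean quite the same thing in both groups. Finally, shifts of 0.03–0.09 SD are below the standard error of an unadjusted contrast: √(2/80) = 0.16 SD with 80 per group, √(2/70) = 0.17 SD with 70. That limits the practical weight of the point, although a bias, unlike sampling error, does not shrink with more participants.

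**Conclusion.** The point holds in a limited form. The filter is one-sided, and the service criteria narrow the gap without closing it. Any IG member with another answer lacks a comparator, and weighting the full IG cannot balance the item for them. Whether this affects the result depends on the IG's answers, which the documents do not give. The 6–18% figure rests entirely on the assumed 10–30% share and 0.3 SD difference.

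It would be tempting to conclude that the restricted comparison should replace the main analysis. The documents do not support that either. The objective is the effect of an existing service under ordinary conditions, 'Objectives' does not limit the question to people without any activity, and the IG's answers may be coloured by the decision already made. A prespecified companion analysis is the proportionate response.

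**What to change.** 1. Report the distribution of the IG's baseline answers to the activity item.
2. Keep the full-group analysis. Beside it, prespecify a key comparison, for the outcomes and for the ICER, restricted to IG members who gave the CG's answer. Within that set, weight on the other covariates and leave this item out of the propensity model, since it no longer varies.
3. State in advance that if the two analyses differ, the conclusion is limited to the restricted population.

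**Cost.** No new data are needed. The restricted comparison has fewer IG members, with the power loss tabulated above: at 30% attrition it falls below 80% once more than about 16% are excluded. It also describes a narrower population than all new service users. Because the IG answers after the service decision, that timing should be reported as a limitation of the restricted set.
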